## Abstract

**Objective:**

Bone grafting is an important surgical procedure to restore missing bone in patients with alveolar cleft lip/palate, aiming to stabilize either sides of the maxillary segments by inducing new bone formation, and in bilateral cleft cases also to stabilize the pre-maxilla. Polyphosphate (PolyP), a physiological polymer composed of orthophosphate units linked together with high-energy phosphate bonds, is a naturally existing compound in platelets which, when complexed with calcium as Ca-polyP microparticles (Ca-polyP MPs), was proven to have osteoinductive properties in preclinical studies.

**Aim:**

To evaluate the feasibility, safety, and osteoinductivity of Ca-polyP MPs as a bone-inducing graft material in humans.

**Methods:**

This prospective non-blinded first-in-man clinical pilot study shall consist of 8 alveolar cleft patients of 13 years or older to evaluate the feasibility and safety of Ca-PolyP MPs as a bone-inducing graft material. Patients will receive Ca-polyP graft material only or Ca-polyP in combination with biphasic calcium phosphate (BCP) as a bone substitute carrier. During the trial, the participants will be investigated closely for safety parameters using radiographic imaging, regular blood tests, and physical examinations. After 6 months, a hollow drill will be used to prepare the implantation site to obtain a biopsy. The radiographic imaging will be used for clinical evaluation; the biopsy will be processed for histological/histomorphometric evaluation of bone formation.

**Discussion:**

This is the first-in-man study evaluating the safety and feasibility of the polyP as well as the potential regenerative capacity of polyP using an alveolar cleft model.

**Trial registration:**

Indonesian Trial Registry INA-EW74C1N. Registered on 12 June 2020

## Background

Alveolar cleft is a defect occurring as a result of the failure of regular development during frontonasal prominence growth, which mostly affects the site between the lateral incisor and the canine (Von Eiselsberg F., 1901). In 1901, the alveolar bone cleft defect was first reconstructed by von Eiselsberg using an autogenous bone graft, while Lexer published in 1908 the first reconstruction with nonvascular graft material [1, 2]. The autogenous bone most often derived from the cancellous iliac crest is still considered as a golden standard for the grafting procedure. Other sources such as the tibia, mandibular symphysis, rib, and the cranium are still being used by surgeon preference [3–7]. However, the drawback of autogenous graft is that it requires another surgical site, which may be associated with post-operative complications [8]. Consequently, the development of effective bone graft substitutes is currently being given high priority and attention [9, 10].

[name] and colleagues identified a new bone graft based on polyphosphate (polyP) [11, 12]. PolyP is a naturally existing compound in the platelets [13]; a physiological polymer composed of orthophosphate units linked together with high-energy phosphate bonds similar to ATP [14]. Complexed with calcium as Ca-polyP microparticles (Ca-polyP MPs), it was proven to have osteoinductive properties in preclinical studies [14–16]. PolyP is also used as a food additive (E 452) and in cosmetics [17]. As such, polyP is considered a safe material in current human applications [18].

Biphasic calcium phosphate (BCP) is a mixture of hydroxyapatite (HA) and β-tricalcium phosphate (β-TCP) with different ratios [19]. BCP in some reports showed intrinsic osteoinductive properties causing ectopic bone formation [20, 21]. While other reports such as de Lange et al. showed that BCP has osteoconductive properties facilitating the bone formation and remodeling in a maxillary sinus lift model [22].

The aim of the current phase I clinical protocol study is to test the safety and feasibility of amorphous Ca-polyP MPs as a graft material.

## Objective

The protocol of this study as presented here is first-in-human.

### Primary objective

The primary objective is to assess the safety of amorphous Ca-polyP MPs as a graft material in the human alveolar cleft reconstruction model.

### Secondary objective

The secondary objective is to evaluate the feasibility and the potential regenerative capacity of polyP using an alveolar cleft model amorphous Ca-polyP MPs.

We hypothesize that the bony reconstruction with osteoinductive Ca-polyP MPs, either or not in combination with BCP granulate, will accelerate the quantity and quality of bone formation in a timely manner. Further, it will reduce the surgical time and morbidity by the absence of a donor site, thereby increasing the cost-effectiveness and quality of care.

## Methods and design

### Ethics

The clinical trial was approved by the Ethics and Research Committee of Faculty of Medicine, Hasanuddin University, Makassar, Indonesia, with code number 1063/UN4.6.4.5.31/PP36/2019. Participants will be recruited from general practices of Hasanuddin Dental Hospital and in the area around Makassar. The trial will be conducted in Hasanuddin Dental Hospital. All participants shall be asked to sign an informed consent. This study complies with the principles of the Declaration of Helsinki.

### Eligibility criteria

#### Inclusion and exclusion criteria

After written informed consent will be obtained by a research team member, the participant will be screened further for eligibility. Patients should be ≥ 13 years old, healthy male or female patients with an alveolar cleft bone defect, non-smoker, with no history of previous grafting procedure(s), with a normal blood count, and with an ASA1 regarding anesthetic risks.

Patients will be excluded when they have poor oral hygiene with mouth plaque, are over 70 years old, are classified as ASA3 and beyond, have local infection and active systematic disease, or received radiotherapy, chemotherapy, immunosuppressive, or anticoagulant therapy recently. Other exclusion criteria comprise having received bone morphogenetic protein (BMP) growth factors or other bone growth-promoting factor therapy, obvious malnutrition, and active influenza.

#### Withdrawal of participants

Participants can leave the study at any time for any reason without any consequences. The investigator can decide to withdraw a subject from the study for urgent medical reasons. When participants withdraw prior to grafting intervention, they will be replaced. Furthermore, if a membrane has been used for any reason, the patient will be considered as a dropout and will be replaced.

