### Intervention

Under general anesthesia, and after local infiltration with adrenaline 1:100,000, an incision will be made at the cleft margin to create a pocket-like tissue towards the nose and the mouth in order to reconstruct the nasal floor as well as the palatal tissue. The goal of this approach is to get rid of the oro-nasal fistula and to expose the bony edges on both sides of the cleft. Under sterile conditions, either Ca-polyP MP alone (NanotecMARIN GmbH, Mainz, Germany) or a combination of BCP (Straumann Bone Ceramic, Villeret, Switzerland) and PolyP will be mixed with normal saline in a ratio of 1 g:1.5 ml and 1 g:2 g:3–5 ml, respectively. A homogenous mixture should be reached before placing the graft material into the cleft defect. A good adaptation of bone graft material should be considered while placing it in the cleft defect. No membrane will be used. A different graft quantity will be considered for larger defects, however, with the same mixing ratios. Absorbable sutures with 3/0 Vicryl for the mucosa and 4/0 Vicryl for the nasal reconstruction will be used for closure.

Post-operative, suitable antibiotics and painkillers will be prescribed to all patients.

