### Sample size

Since this is a first-in-man trial, the current trial sample size has been limited to only 2 × 4 patients, with the primary goal to gain a first insight on the safety and feasibility of the treatment with Ca-polyP. It is assumed that no SAEs or AEs will occur, and then, an n = 4 for each group should therefore be sufficient.

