### Randomization and treatment allocation

Because this is a first-in-human study, it is not possible to keep all personnel blinded to the assignment group. After written informed consent will be obtained by the main surgeon, randomization will be performed with regard to the treatment group. Central randomization using a randomization program on a secure computer will be used after the completion of patient enrollment. Patients will receive a unique study code, and their data will be provided to the clinical and research evaluators in a patient-coded manner.

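### The membrane rule can take patients already exposed to a first-in-human graft out of the safety and feasibility results, and nothing in the protocol says that they still count

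*Protocol article*

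**What the plan says.** Withdrawal of participants contains two replacement rules. The first covers patients who leave before treatment: "When participants withdraw prior to grafting intervention, they will be replaced". The second follows as an addition: "if a membrane has been used for any reason, the patient will be considered as a dropout and will be replaced".

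The Intervention section states "No membrane will be used". That sentence comes after the instructions on placing and adapting the graft and before those on closure.

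The Primary objective section reads: "The primary objective is to assess the safety of amorphous Ca-polyP MPs as a graft material in the human alveolar cleft reconstruction model". Under Secondary objective: "The secondary objective is to evaluate the feasibility and the potential regenerative capacity of polyP". On size, the Sample size section says that "the current trial sample size has been limited to only 2 × 4 patients".

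The safety part of Outcomes sets the decision rule. One serious adverse event (SAE) is enough for polyP not to be judged safe for now. Other adverse events (AEs) are acceptable if they are no more frequent than under standard care with autologous bone, or can be resolved by conventional non-invasive means, or both.

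**The concern.** In a first-in-human study with safety as the primary objective, the results should cover everyone who was exposed. The membrane rule selects on something that happens after randomisation, during the operation. It calls the patient a dropout whatever the reason was, and fills the place with someone else. The abstract describes the study as non-blinded, and the Blinding section covers only the radiologist and the histopathologist, so the operator whose decision triggers removal knows the treatment.

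Whether the graft can be placed and closed over as planned is itself information about feasibility. If departures from the planned procedure are replaced until 8 patients without a departure are available, the feasibility result is favourable partly by construction. If membrane use is also linked to how the patient fares, the safety result shifts in the same direction.

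**Working it through.** **Inputs**
- Planned size: 2 × 4 = 8 (Sample size; Study design and Trial status agree). This is a pragmatic limit without a power or precision formula, so there is nothing further to reproduce.
- Decision rule: safety part of Outcomes, as summarised above.
- Membrane rate: not in the documents. Assumed here at 5% to 30%.

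**Step 1: does the rule reach exposed patients?** The first replacement rule is limited to the time before grafting. The second is separate from it and has no time limit. A membrane is mentioned only in the operative description, next to graft placement. Randomisation precedes the operation: "Central randomization using a randomization program on a secure computer will be used after the completion of patient enrollment". The rule therefore acts after randomisation, and nothing confines it to patients who have not received Ca-polyP.

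**Step 2: does another section put them back?**
- Study design: adverse events are documented at each follow-up visit. It does not say that replaced patients are included in the report.
- Adverse event section: any adverse event is graded, and an SAE is notified to the sponsor within 24 h. This concerns recording, not who is counted.
- Post-trial care: all participants are followed for 3 years for safety. This lies outside the 6-month endpoint.
- Safety part of Outcomes: it names no denominator.

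None of these states that a membrane patient counts in the 6-month safety conclusion or in the feasibility result.

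**Step 3: what can one uncounted patient do?** Suppose 9 patients are grafted, and one of them receives a membrane, has an event and is replaced. The one-sided 95% exact upper bound for x events in n patients is the 0.95 quantile of Beta(x + 1, n − x). For x = 0 it is 1 − 0.05^(1/n).

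| Who is counted | Events | Rate | Upper bound |
|---|---|---|---|
| Membrane patient dropped, whole trial | 0/8 | 0% | 1 − 0.05^(1/8) = 31.2% |
| All exposed, whole trial | 1/9 | 11.1% | 42.9% |
| Membrane patient dropped, one arm | 0/4 | 0% | 1 − 0.05^(1/4) = 52.7% |
| All exposed, one arm | 1/5 | 20.0% | 65.7% |

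If the event is an SAE, counting it changes the conclusion under the protocol's own rule. If it is another adverse event that did not resolve by non-invasive means, the frequency comparison decides. The rate 1/9 exceeds any standard-care rate below 11.1%; 0/8 exceeds none.

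**Step 4: how often would a patient be dropped?** With membrane rate m, the chance of at least one among the first 8 treated is 1 − (1 − m)^8. The expected number exposed but uncounted while 8 places are filled is 8m/(1 − m).

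| Assumed m | At least one of 8 | Expected uncounted |
|---|---|---|
| 5% | 1 − 0.95^8 = 34% | 0.4 |
| 10% | 1 − 0.90^8 = 57% | 0.9 |
| 20% | 1 − 0.80^8 = 83% | 2.0 |
| 30% | 1 − 0.70^8 = 94% | 3.4 |

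**The case against.** The strongest reply is that being replaced is not the same as being deleted. A sponsor may replace a patient to keep 4 evaluable per arm and still report everyone exposed. The sections on adverse events, study design and post-trial care lean that way, and the definition of analysis populations is often left to a fuller document. This stands in part: the text does not say that events in these patients go unreported, and a reader who infers that goes beyond it. However, the protocol itself fixes the dropout label and the replacement, and never says that the patient remains in the safety conclusion. This is a stated rule with a harmful natural reading, not a missing detail.

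Four stronger readings are tempting and are not supported:

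- *Membranes would be used because the graft was not contained, the wound could not be closed or it broke down.* The documents give no reasons for membrane use. The rule may simply guard against a co-treatment that confounds bone formation. That would justify leaving membrane cases out of a radiographic or histological summary, but not out of safety.
- *The trial would report no events when there were several.* Such an outcome needs an invented overlap between membrane use and events. It is also partly blocked: an SAE of severe toxicity or infection at the graft site ends the trial, so no replacement would follow. The 1/9 against 0/8 example therefore concerns other SAEs and adverse events.
- *A replacement fills a known, vacated arm.* Randomisation follows completed enrolment, but the article does not say how replacements are allocated. It also differs on who takes consent (a research team member under Eligibility criteria, the main surgeon under Randomization and treatment allocation).
- *The randomised comparison is the main casualty.* The safety conclusion is about polyP as a whole, so damage to the comparison between arms is secondary.

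**Conclusion.** The point holds in this form: as written, the membrane rule can remove patients exposed to Ca-polyP from the safety and feasibility results after randomisation, and no section states that they still count.

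Two steps are inferred: that the graft is already in place, or being placed, when the membrane is used; and that a replaced dropout is absent from the results. Both are the natural reading, and no section contradicts them.

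The consequence can be large because the trial is small: one uncounted event is the difference between 11.1% and 0%, and can change the safety conclusion. How likely that is cannot be known from the documents. It depends on an unstated membrane rate and on whether membrane use and events go together. No membrane use is planned, so the effect may be nil.

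**What to change.** Amend the membrane sentence under Withdrawal of participants along these lines:

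> Every patient who received any Ca-polyP remains in the safety and feasibility results in the randomised arm. Follow-up continues, subject to the participant's right to withdraw. Membrane use is reported with its reason, as a deviation relevant to feasibility. A grafted patient in whom a membrane was used may be replaced only to complete the set evaluable for radiography and histology.

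Replacement after withdrawal before grafting can stay as it is. Allowing replacement for the evaluable set keeps the planned 4 + 4 without membrane, and does not put at risk the minimum of 3 biopsied patients per group in the histology section. The amendment concerns who is counted, not whether a membrane should be used.

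Cost: one paragraph, with no patients or procedures beyond the replacements already foreseen. The adverse event and feasibility figures may look slightly less favourable, and the safety denominator may exceed 8.

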### Intervention

Under general anesthesia, and after local infiltration with adrenaline 1:100,000, an incision will be made at the cleft margin to create a pocket-like tissue towards the nose and the mouth in order to reconstruct the nasal floor as well as the palatal tissue. The goal of this approach is to get rid of the oro-nasal fistula and to expose the bony edges on both sides of the cleft. Under sterile conditions, either Ca-polyP MP alone (NanotecMARIN GmbH, Mainz, Germany) or a combination of BCP (Straumann Bone Ceramic, Villeret, Switzerland) and PolyP will be mixed with normal saline in a ratio of 1 g:1.5 ml and 1 g:2 g:3–5 ml, respectively. A homogenous mixture should be reached before placing the graft material into the cleft defect. A good adaptation of bone graft material should be considered while placing it in the cleft defect. No membrane will be used. A different graft quantity will be considered for larger defects, however, with the same mixing ratios. Absorbable sutures with 3/0 Vicryl for the mucosa and 4/0 Vicryl for the nasal reconstruction will be used for closure.

Post-operative, suitable antibiotics and painkillers will be prescribed to all patients.

### Adverse event (AE) and serious adverse event (SAE)

Any adverse event will be graded with respect to intensity and classified as either serious or non-serious according to the World Health Organization classification. Any change in health which occurs between screening examination and first administration of amorphous Ca-polyP microparticles or related procedures will be recorded as part of the subject’s medical history, and full medical care will be given to all participants. In the case of a SAE, the sponsor will be notified within 24 h from the onset. If the SAE concerns severe toxicity or infection associated with the graft site, the trial will be terminated immediately.

### Sample size

Since this is a first-in-man trial, the current trial sample size has been limited to only 2 × 4 patients, with the primary goal to gain a first insight on the safety and feasibility of the treatment with Ca-polyP. It is assumed that no SAEs or AEs will occur, and then, an n = 4 for each group should therefore be sufficient.

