### Outcomes

#### Safety assessment based on physical examination and laboratory measurements

When a SAE occurs, it will be concluded that polyP is not (yet) safe in the current setting. For AEs, if they do not occur at a higher frequency than in patients treated with standard care (autologous bone) and/or can be resolved by non-invasive conventional methods (e.g., analgesics, antibiotics), the polyP product will be considered safe. In all other cases, polyP will not be considered safe (yet).

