#### Monitoring

Monitoring will be done constantly by internal monitors of the Ethics and Research Committee of Faculty of Medicine, Hasanuddin University. Since there is a negligible risk, a data safety monitoring board will not be formed. A safety report will be provided to the Medical Research Ethics Committee of the Ethics and Research Committee of Faculty of Medicine, Hasanuddin University, every year. An interim analysis will not be conducted.

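### The claim that four patients per group is sufficient rests on assuming that no adverse events occur, which is circular; the small pilot size itself can stay

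*Protocol article*

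**What the plan says.** The Sample size section of the protocol article makes two separate statements. The first is pragmatic. The trial, being the first in humans, is kept to two groups of four, "with the primary goal to gain a first insight on the safety and feasibility of the treatment with Ca-polyP". The second is an inference: "It is assumed that no SAEs or AEs will occur", from which it concludes that "an n = 4 for each group should therefore be sufficient".

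The Primary objective section makes safety the main question: "The primary objective is to assess the safety of amorphous Ca-polyP MPs as a graft material".

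Two other sections provide for events. The section on adverse events (AEs) and serious adverse events (SAEs) covers grading, notification of the sponsor, and termination of the trial for certain SAEs. Under Outcomes, the safety assessment gives a decision rule. If an SAE occurs, "it will be concluded that polyP is not (yet) safe in the current setting". AEs are compatible with a finding of safe if they are no more frequent than under autologous bone grafting, and/or if they resolve with non-invasive conventional treatment.

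The article gives no target precision, no event rate to be detected and no standard-care AE rate.

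**The concern.** A sample size is sufficient in relation to something it must achieve: a precision, a chance of detecting an event, or the exclusion of a rate. Here the only ground for sufficiency is that nothing will happen. That is the finding the trial is meant to produce, so the argument is circular.

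It also fits poorly with the two sections that set out what to do when AEs and SAEs arise. The size is justified as though those provisions will never be used.

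What is at stake is the reading of a clean result. With no events, nothing in the safety rule is breached and the product would be considered safe. A reader told beforehand that the sample was sufficient could take 0 of 8 as establishing safety, although substantial event rates would not have been excluded.

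**Working it through.** **Inputs from the documents.** Eight patients, four per group, and an assumed event rate of 0 (Sample size); safety as the primary objective (Primary objective).

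**Assumptions made here.** The 95% confidence level for the safety limits, because the article sets none for safety; the illustrative true rates of 10% and 20%; independent patients; and, for the figures on eight, a common event rate in the two graft groups.

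**Step 1: can the stated n be reproduced?** The chance of at least one event in n patients with true rate p is 1 − (1 − p)^n. At the assumed p = 0 this is 1 − 1^n = 0 for every n, whether 1, 4, 8 or 100. The assumption therefore does not lead to 4 or to any other number. The section gives no other quantity from which 4 could be derived.

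**Step 2: what would a clean result exclude?** With zero events in n patients, the exact (Clopper-Pearson) upper limit is 1 − 0.025^(1/n) for a two-sided 95% interval and 1 − 0.05^(1/n) for a one-sided 95% bound.

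| Result | Two-sided 95% upper limit | One-sided 95% upper limit |
|---|---|---|
| 0 of 8 | 1 − 0.025^(1/8) = 36.9% | 1 − 0.05^(1/8) = 31.2% |
| 0 of 4 | 1 − 0.025^(1/4) = 60.2% | 1 − 0.05^(1/4) = 52.7% |

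The label matters. With zero events the lower limit is 0, so the two-sided figure acts as a 97.5% upper bound. A statement that rates are excluded with 95% confidence should use the one-sided column, or say explicitly that the interval is two-sided.

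**Step 3: how often would a real event rate be missed entirely?** The probability of zero events is (1 − p)^n.

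| True rate | Missed in 8 | Missed in 4 |
|---|---|---|
| 10% | 0.9^8 = 43% | 0.9^4 = 66% |
| 20% | 0.8^8 = 17% | 0.8^4 = 41% |

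**Step 4: the passages side by side.** The Sample size section assumes no AEs and no SAEs. The AE/SAE section and the safety assessment say what follows if they occur. Both can stand in one document, because a rule for handling events is not a forecast of them. But a protocol that needs such rules cannot also rest the adequacy of its size on their never being needed.

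**The case against.** The best defence is that the small size does not depend on the faulty sentence. The section opens with a modest reason, a first look in a first-in-man setting, and does not claim power. This stands: eight patients can be reasonable for a pilot, and the fault lies in the inference and the word sufficient. A reader might infer that the trial is too small and must be enlarged. The documents do not support that, since they set no precision target that eight patients fail to meet.

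A second defence is that the safety rule is conditional. It says what follows if AEs occur, and its and/or clause allows AEs that resolve with conventional treatment whatever their frequency. This also stands. It would be too strong to say that the rule forecasts AEs at the standard-care rate and so flatly contradicts the assumption. Nor do the antibiotics and painkillers prescribed to all patients (Intervention) show that AEs are expected, because that is routine postoperative prescribing.

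A third is that precision statements are often left to a full protocol or analysis plan. This is true, and their absence alone would be no finding. But the article does state a justification, and the one it states is invalid.

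Two further inferences are tempting. One is that the Monitoring statement "Since there is a negligible risk, a data safety monitoring board will not be formed" rests on the same assumption. The article does not link the two, and that sentence is a separate matter. The other is that the Conclusion section overclaims safety. It says only what the authors intend to evaluate, so nothing there needs correction on this point.

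**Conclusion.** The point holds for the inference, not for the number of patients. That four per group "for each group should therefore be sufficient" does not follow from assuming no events: the premise is the result sought under the primary objective, and it fits any n.

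The precision actually available after a clean result is an upper limit of 36.9% for all eight patients and 60.2% for one group (two-sided 95%), or 31.2% and 52.7% (one-sided 95%). The choice of convention does not change the conclusion. All four figures are conditional on zero events being observed. The 36.9% and 31.2% also assume that the two graft groups share one event rate.

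A reader might go further and say that the no-event assumption is almost certain to fail. That would need an AE rate for this surgery, and the documents give none.

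**What to change.** In the Sample size section, delete the assumption that no events will occur and the claim of sufficiency drawn from it. Keep the first-in-man rationale and the 2 × 4 patients. Add a statement of precision, for example:

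> If no event is seen, the exact two-sided 95% upper limit for the true event rate is 36.9% for 0/8 and 60.2% for 0/4 (one-sided 95%: 31.2% and 52.7%). An event with a 10% rate would be missed entirely with probability 43% in 8 patients and 66% in 4.

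In the safety assessment under Outcomes, qualify the conclusion so that an absence of events is reported with these limits as a first insight and is not presented as establishing safety.

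The cost is a change of wording. The stated precision will look less favourable than the present text. No patients, visits or endpoints are added.
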